#### Procedure

All participants will be asked to answer the Adapted Fresno Test or the AFT [24] for baseline or pre- assessment of their knowledge and skills to EBP, and the Questions on attitudes to EBP [25], for baseline or pre- assessment of their attitudes to EBP (Figure 1). These tools will be sent through the participants' email, the day before the EBP intervention group's scheduled training.

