#### Identification of reference population of participants

A register will be collated from a) a database of physiotherapists collated by the primary researcher from a preliminary study which established the profile of physiotherapists [18] and b) the registry of the Philippine Physiotherapy Association (PPTA), of which the primary researcher is a member and from whom approval has been sought and granted.

Physiotherapists who will express their interest in participating in the study will complete an information sheet which includes age, gender, years in practice, and highest educational attainment. There is also a screening component of the questionnaire which will seek information on any EBP training program. This section is particularly important as participants should not have been exposed to a formal EBP course or training to minimize the potential influence of such to the outcomes. To be specific, they should not have attended lectures and workshops on clinical question formulation, database searching, critical appraisal and applying findings on patient cases. Once screened for eligibility, participants will be asked to attend a meeting to orient them to the procedures of the study and to obtain written informed consents.

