#### Randomisation and blinding

An independent researcher will randomly allocate participants into either the EBP training group or a waitlist control group, using a computer generated random numbers. Allocation into treatment and control groups will be undertaken by an independent research assistant who is unaware of the study objectives and the participants. The schedule of training will depend on the group allocation, such that those in the intervention group will have their training earlier than the waitlisted control group. Participants and assessors of the study outcomes will be blinded to the allocation at all times.

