**Figure 1 F1:**
[figure not shown]
**Flow of procedures**.

The EBP intervention group will attend a one day training (Additional File 1) in a training centre at the University of Santo Tomas, Philippines. The objectives of the training will be provided to the participants before each of the six lectures and the practical sessions. Small group discussions will occur between the lectures, to enhance learning opportunities for participants. A checklist to assist participants to apply the evidence developed for this study will be provided as a take-home recommendation form, to guide the application of evidence in actual patient cases (Figure 2). After the EBP training, a link to an online support will be introduced to the participants. This has been developed to assist the participants in their EBP-related activities post training, as follow up support and multifaceted interventions have more potential to influence clinicians' behaviour to using evidence in practice [2]. This online support is further described in the intervention section of this document. Activity diaries will also be provided to participants to log their EBP-related activities when faced with a new or unique case, and provide their comments to their activities for a period of three months for short term EBP behaviour assessment.

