**Figure 2 F2:**
[figure not shown]
**EBP Checklist**.

At the end of the training, participants will be asked to provide a second set of answers to the Adapted Fresno test and the Questions on attitudes to EBP for post EBP training intervention assessment.

The waitlist control group will undergo the pre and post- knowledge, skills and attitude test at the same period as the intervention group. There will be no training for the control group during this time. However, for the next three months, they will also be provided with activity diaries to log their activities as basis for their treatment when faced with a new or unique case, whether these activities are EBP-related or not.

Three months post EBP training, a third set of answers to the Adapted Fresno test and the Questions on attitudes to EBP, will be obtained from both groups to measure if knowledge, skills and attitudes to EBP were sustained over the three month period in the EBP intervention group and to measure the stability of knowledge, skills and attitudes to EBP of the control group.

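### The knowledge and attitude baselines are collected after randomisation, when the intervention arm very likely knows its training date, so they can depend on allocation

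*Protocol article*

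**What the plan says.** All places are in the Methods of the protocol article.

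- **Identification of reference population of participants.** After screening, "participants will be asked to attend a meeting to orient them to the procedures of the study and to obtain written informed consents". Age, gender, years in practice and education are recorded earlier, when a physiotherapist expresses interest.
- **Randomisation and blinding.** On how dates are set: "The schedule of training will depend on the group allocation, such that those in the intervention group will have their training earlier". Controls are trained later. The paragraph closes by asserting that neither participants nor outcome assessors will know the allocation at any point.
- **Procedure.** Both arms take the AFT, as the baseline for knowledge and skills, and the attitude questions. On timing: "These tools will be sent through the participants' email, the day before the EBP intervention group's scheduled training". The course itself lasts one day and is held in person at a university training centre, for the intervention arm only. Controls take the pre- and post-tests over the same period, without training.
- **Plan of analysis.** Changes in outcomes are compared between the groups with means and 95% confidence intervals. Baseline comparisons are used to establish that the groups are comparable.

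**The concern.** A baseline measured before allocation cannot be influenced by it. Here the two baselines that matter for the knowledge, skills and attitude outcomes are timed by reference to an intervention group that already has a training date. Both instruments are sensitive to the respondent's state of mind: one is a test that rewards effort, the other a set of seven self-rated opinions. Someone who expects a course the next day may prepare, may not bother, or may report a different attitude from someone who has been told to wait. The choice to return the emailed forms at all may also differ.

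At stake is the between-group comparison of change. The baseline is subtracted from the later score, so a difference in baseline caused by allocation becomes a difference in change even if the training does nothing. The planned baseline comparison is no safeguard, because it would examine a measurement that allocation may already have altered. Since the problem arises when the data are collected, a later analysis plan can reduce it but cannot fully remove it.

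**Working it through.** **Step 1: order of events.** The date of training is set by allocation (Randomisation and blinding). The baseline is sent the day before the date set for the intervention group (Procedure). A group with its own date can exist only once allocation has been made, so the baseline comes after randomisation. This follows from the content of the two statements, not from the order of the article's sections.

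**Step 2: awareness.** The intervention group travels to a one-day course on the day after the email, so its members must have their date by about then. All participants have been oriented to the study procedures. The blinding statement points the other way, but no means is described of keeping an early-trained group unaware of its schedule.

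**Step 3: effect on the estimate.** Let s be the shift, in SD units, that allocation causes in the intervention arm's measured baseline only, and ρ the pre-post correlation. The post score is taken as unaffected.

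- Change-score comparison: bias = −s.
- ANCOVA on baseline: bias ≈ −ρs.

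With a true effect equal to the 0.6 target and ρ = 0.5:

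| s | Change score | ANCOVA |
|---|---|---|
| +0.1 | 0.6 − 0.1 = 0.50 | 0.6 − 0.05 = 0.55 |
| +0.2 | 0.6 − 0.2 = 0.40 | 0.6 − 0.10 = 0.50 |
| +0.3 | 0.6 − 0.3 = 0.30 | 0.6 − 0.15 = 0.45 |

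A negative s inflates the estimate by the same amounts.

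**Step 4: type I error with no true effect.** Inputs: n = 27 per group and two-sided 5% (Sample Size determination); ρ = 0.5 and s are assumptions, as the protocol gives neither.

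- Change score: SD = √(2(1 − 0.5)) = 1, SE = √(2/27) = 0.272.
- ANCOVA: residual SD = √(1 − 0.5²) = 0.866, SE = 0.866 × 0.272 = 0.236.
- For a shift of 0.2: noncentrality is 0.20/0.272 = 0.73 for change scores and 0.10/0.236 = 0.42 for ANCOVA. The noncentral t distribution gives rejection rates of 11.1% and 7.0%.

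| Shift (either sign) | Change score: bias, noncentral t, simulation | ANCOVA: bias, noncentral t, simulation |
|---|---|---|
| 0.1 | 0.10, 6.5%, 6.8% | 0.05, 5.5%, 5.2% |
| 0.2 | 0.20, 11.1%, 10.9% | 0.10, 7.0%, 6.8% |
| 0.3 | 0.30, 19.1%, 18.9% | 0.15, 9.6%, 9.4% |

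The simulation used 4,000 trials per row and agrees with the formula to within Monte Carlo error.

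**The plan's own figure.** The 27 per group serves here only as the planned size. A two-sample, two-sided formula for an effect of 0.6 gives 2 × ((1.96 + 0.84)/0.6)² = 43.6, that is 44 per group, so 27 does not reproduce. That is a separate matter and does not affect this point.

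**The case against.** The strongest objection is that the protocol never says when participants learn their allocation or date, and it states that they are blinded throughout. Figure 1, the flow of procedures, is not available to settle the order. This stands in part: awareness is an inference and should be called one. It does not remove the point, because an unexplained assertion of blinding sits badly with a schedule that depends on allocation and with attendance the next day. The sections need reconciling on either reading.

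A second objection is that no document supports a shift of 0.2 or 0.3 SD or a correlation of 0.5, that the direction is open, and that ANCOVA roughly halves the bias at that correlation. All of this stands. Less effort before training would inflate the effect, and preparation would shrink it, although one day leaves little time to prepare. A comparison of post-training scores alone would not carry the shift. The protocol, however, describes a comparison of changes.

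Three stronger readings are tempting but unsupported:

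- **Looked-up answers.** A reader might infer that an emailed test with no supervision described biases the comparison. Both arms receive the same email, so looking up answers is not in itself tied to allocation.
- **Different test conditions afterwards.** The post-test is placed as follows: "At the end of the training, participants will be asked to provide a second set of answers to the Adapted Fresno test". A reader might infer that controls sit it by email under other conditions. The protocol fixes only the period for controls, and an article may leave the mode to the full document.
- **Failure of intention to treat.** A reader might infer that waitlisted people who return no baseline are dropped. Nothing says so, and the handling of missing data is commonly left to the analysis plan.

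**Conclusion.** The concern holds in a limited form. By the stated procedure, the AFT and attitude baselines follow randomisation, and intervention participants very likely know their date when they answer. The baseline can therefore depend on arm, and any such shift passes in full into the change-score comparison. The protocol does not show that a shift will occur, how large it would be or which way it would go.

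The illustration for a 0.2 SD shift (bias of 0.20 SD, one third of the 0.6 target, and about 11% type I error; about 0.10 SD and 7% with ANCOVA) rests on the assumed shift, the assumed correlation of 0.5, and a shift that touches the baseline measurement alone.

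The scope is also limited. The demographic items are collected before allocation, and the activity diaries have no pre-training measurement. Only the two instruments sent by email are exposed.

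**What to change.** Have every participant complete the AFT and attitude baselines before allocation is generated, or at least before the allocation or the training date is disclosed. The existing orientation and consent meeting is a natural occasion ("participants will be asked to attend a meeting to orient them to the procedures of the study"). Amend Procedure to state this order. Reconcile it with Randomisation and blinding by saying when participants learn their date, and what, if anything, they are kept unaware of. Supervised testing is not needed for this repair.

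The cost is a somewhat longer meeting and a longer interval between baseline and training. No sample-size figure changes. Adjusting for baseline by ANCOVA would lessen the bias if the order cannot be changed, but would not remove it.

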**Figure 1 F1:**
[figure not shown]
**Flow of procedures**.

The EBP intervention group will attend a one day training (Additional File 1) in a training centre at the University of Santo Tomas, Philippines. The objectives of the training will be provided to the participants before each of the six lectures and the practical sessions. Small group discussions will occur between the lectures, to enhance learning opportunities for participants. A checklist to assist participants to apply the evidence developed for this study will be provided as a take-home recommendation form, to guide the application of evidence in actual patient cases (Figure 2). After the EBP training, a link to an online support will be introduced to the participants. This has been developed to assist the participants in their EBP-related activities post training, as follow up support and multifaceted interventions have more potential to influence clinicians' behaviour to using evidence in practice [2]. This online support is further described in the intervention section of this document. Activity diaries will also be provided to participants to log their EBP-related activities when faced with a new or unique case, and provide their comments to their activities for a period of three months for short term EBP behaviour assessment.

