#### EBP behaviour

EBP behaviour will be measured in two ways: (1) activity diaries to be provided to all participants, both intervention and waitlist groups, in paper and electronic copies, and (2) frequency of logging in, in the online support for the EBP intervention training participants http://www.unisa.edu.au/cahe/Resources/EBPPhil/default.asp, considered as an electronic EBP learning portfolio. As it is not possible to conduct actual participant observation in practice, activity diaries are commonly used to log and report participants' activities in EBP [37]. The electronic EBP learning portfolio on the other hand, which according to the literature, are both educational intervention and an evaluation strategy," *is the most promising approach to document actual performance of EBP steps *"[37].

The frequency of conducting non-EBP (asking a peer, reviewing a textbook etc) and EBP-related activities (drafting a clinical question in PICO form, searching the literature for the evidence, undertaking critical appraisal and applying the evidence found) will be logged in the activity diaries provided to the participants. The frequency of conducting these activities and the frequency of logging in the online support provided will be counted and interpreted as behaviour measures. Behaviour measures will be interpreted in two ways, evidence-seeking behaviour and practice-change behaviours ref. Activities which relate only to drafting a clinical question, searching and appraising the evidence, are classified as evidence-seeking behaviours. Applying the evidence to an actual patient case is classified as a measure of practice-change behaviour [38].

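### The diary instruction is worded differently by arm and conflicts with the outcome definition, so non-EBP and total activity counts may not be comparable between groups

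*Protocol article*

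**What the plan says.** Three places in the protocol article describe the activity diary.

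- **Procedure, intervention group** (text after Figure 1): "Activity diaries will also be provided to participants to log their EBP-related activities when faced with a new or unique case". The period is three months.
- **Procedure, waitlist control group** (text after Figure 2): these participants are to "log their activities as basis for their treatment when faced with a new or unique case, whether these activities are EBP-related or not". The period is again three months.
- **Outcome measures, EBP behaviour**: the diaries are described as "activity diaries to be provided to all participants, both intervention and waitlist groups, in paper and electronic copies". On content, the section says "The frequency of conducting non-EBP (asking a peer, reviewing a textbook etc) and EBP-related activities" "will be logged in the activity diaries provided to the participants", and it draws no distinction by arm.

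The same outcome section states how the data are used: "The frequency of conducting these activities and the frequency of logging in the online support provided will be counted and interpreted as behaviour measures". It then names two interpreted classes. For the first: "Activities which relate only to drafting a clinical question, searching and appraising the evidence, are classified as evidence-seeking behaviours". For the second: "Applying the evidence to an actual patient case is classified as a measure of practice-change behaviour". The Plan of analysis foresees comparisons within and between groups.

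**The concern.** A between-group comparison of self-reported counts is sound only if both groups are asked to record the same things. Here the request as worded depends on allocation: one group is asked for EBP-related activities, the other for EBP-related and other activities alike. A difference in recorded non-EBP or total activity could then come from the instruction and not from the training.

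The point carries weight for three reasons. Behaviour is one of the four outcome domains in the study aims. The other behaviour measure, log-ins to the online support, is defined only for the intervention group, so the diary is the only behaviour measure shared by the arms. And the diaries begin after training, with no pre-training diary described, so there is no baseline value against which a recording difference could be seen or adjusted. An activity that was never logged cannot be recovered afterwards.

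**Working it through.** The protocol gives no figure on this point to reproduce. The check sets the texts side by side and follows each reading to its consequence.

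**Step 1. What each text requests.**

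| Text | Group | EBP-related activities | Non-EBP activities |
|---|---|---|---|
| Procedure, after Figure 1 | Intervention | Requested | Not mentioned |
| Procedure, after Figure 2 | Control | Requested | Requested |
| EBP behaviour | Both | Logged and counted | Logged and counted |

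The trigger (a new or unique case) and the three-month period are the same in both arms. Only the requested content differs. The second and third rows agree; the first is narrower than both.

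**Step 2. Which counts are affected.**

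- Evidence-seeking count (question, search, appraisal): EBP-related items only, requested in both arms under every text.
- Practice-change count (applying the evidence to a patient): also EBP-related, requested in both arms under every text.
- Non-EBP count: requested in the control arm, but not in the intervention arm under the Procedure wording.
- Total count: inherits the problem of the non-EBP count.
- EBP share of all activities: inherits it too, but the protocol does not define or plan this measure.

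**Step 3. An illustration with assumed numbers.** Suppose that participants in each arm truly carry out 4 EBP-related and 6 non-EBP activities, so there is no true difference. Suppose that the control arm logs everything and the intervention arm logs all 4 EBP-related activities plus a fraction *f* of the 6 others. The intervention arm then records 6*f* non-EBP activities, a total of 4 + 6*f*, and an EBP share of 4/(4 + 6*f*).

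| Recorded | Intervention, *f* = 0 | Intervention, *f* = 0.5 | Intervention, *f* = 1 | Control |
|---|---|---|---|---|
| EBP-related | 4 | 4 | 4 | 4 |
| Non-EBP | 0 | 3 | 6 | 6 |
| Total | 4 | 7 | 10 | 10 |
| EBP share | 4/4 = 100% | 4/7 = 57% | 4/10 = 40% | 4/10 = 40% |

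The column *f* = 0 treats the Procedure sentence as excluding everything else. The column *f* = 1 is the content that the EBP behaviour section describes. The documents do not say which would occur. The distortion in the non-EBP and total counts runs in one direction over the whole range below *f* = 1, while the EBP-related count is unaffected by *f*.

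**Step 4. Completeness of the EBP-related entries.** If the arms log fractions *r*_I and *r*_C of their true EBP-related activities, the recorded ratio of counts equals the true ratio times *r*_I/*r*_C. A prompt directed at EBP in one arm and at all activities in the other gives a reason why the two fractions might differ. The documents give no basis for the size of that difference, so no number can be attached.

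**The case against.** The strongest reply is that the outcome section governs. It describes one diary for all participants with the same content in both arms, and the Procedure sentence may be loose narrative. That sentence does not say that other activities are to be left out. The diary form is not shown, and participants would follow the form. All of this is fair. It means that an arm-specific diary is not established, and that zero recorded non-EBP activities in the intervention arm is an extreme case. It does not remove the conflict: if the outcome section governs, the Procedure sentence is wrong; if the Procedure sentence governs, the planned non-EBP count does not exist in the intervention arm. Either way a text must change.

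A reader might go further and infer that no diary frequency can be compared between the arms, or that the form would manufacture an apparent behaviour change. The documents do not support that. Both interpreted classes consist solely of EBP-related activities, which are requested in both arms in all three places, and the illustration gives 4 versus 4 on those. The striking contrast of 100% with 40% concerns a share that the protocol does not plan to report. The control instruction also mentions EBP-related activities by name, so the difference in prompting is one of emphasis.

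**Conclusion.** The point holds in limited form. The intervention-arm instruction in the Procedure section is narrower than the control-arm instruction and contradicts the EBP behaviour section. Followed literally, it makes the non-EBP count and the total count non-comparable between arms, together with any share built from them. The evidence-seeking and practice-change counts remain defined in both arms; for them there is a possibility of differential reporting whose size cannot be judged from the documents.

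The figures in the illustration rest on assumed activity levels and on how strictly intervention participants would read the sentence; they show the direction, not an estimate. The conclusion about the texts needs no such assumption. Because the diary is the only behaviour measure common to both arms and lost entries cannot be restored, the matter should be settled before diaries are issued.

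**What to change.** Amend the intervention-arm sentence in the Procedure section so that it matches the control-arm sentence and the EBP behaviour section. Use one identical diary and one identical instruction in both arms: for each new or unique case, log every activity used as a basis for treatment, EBP-related or not, from the same list. If the forms in use are already identical, stating this in the Procedure section is enough.

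The cost is one reworded sentence, a check of the form, and slightly more logging by the intervention group. Recording the number of new or unique cases, so that activities can be expressed per case, would be a reasonable addition but is optional: the mismatch in wording does not require it.
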